The primary objective of this pilot study is to evaluate the feasibility and acceptability of integrating PROMBot-HSM-AF, a chatbot-based platform for collecting PROMs and clinical parameters, into routine post-ablation follow-up care at a tertiary hospital. The specific aims, framed for the feasibility and pilot phase, are to: (1) quantify recruitment, retention, and engagement rates over the 3-month follow-up and compare each against pre-specified progression thresholds (retention ⩾80%, engagement ⩾70%), constituting the primary outcomes; and, as secondary, exploratory outcomes, (2) assess the usability and acceptability of the chatbot (patients) and of the clinical monitoring interface (healthcare professionals) at 3 months, using validated usability measures (System Usability Scale [SUS], Post-Study System Usability Questionnaire [PSSUQ]), behavioral indicators, and semi-structured interviews; and (3) evaluate the preliminary integration and data completeness of PROMs (e.g., Atrial Fibrillation Effect on Quality-of-Life [AFEQT]) collected via the platform over the 3-month follow-up, and explore between-group differences as hypothesis-generating estimates to inform a definitive trial.

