### Sample size

2.4

This pilot was sized to estimate feasibility parameters, not clinical efficacy. Using G*Power 3.1, sample sizes were derived from one-sided proportion tests (80% power, α=0.05) for retention and engagement; the one-sided test reflects the directional progression criteria, where only meeting or exceeding the thresholds is relevant. Thresholds were retention ⩾80% and engagement ⩾70%, yielding 62 and 56 participants, respectively; allowing for 20% dropout, the final target was 76 (38 per group). Both the directional hypothesis and the ⩾70% threshold are consistent with adherence benchmarks for feasibility pilots (27) and with retention and engagement rates reported in a comparable cardiovascular RPM intervention (e.g., 71%–94% sustained activity/survey completion over six months) (28).

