#### Primary outcomes (feasibility)

2.9.1

The primary outcomes of this trial are feasibility parameters, including recruitment rate (eligible patients providing consent), retention rate (participants completing the 3-month follow-up), and engagement rate (proportion of chatbot prompts answered within 24 h) (36, 37).

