#### Quantitative data

2.10.1

Participant characteristics and study outcomes will be summarized using descriptive statistics. Continuous variables (e.g., age, body mass, blood pressure) will be reported as means ± SDs or medians [IQR], depending on distribution, while categorical variables (e.g., sex, educational level, comorbidities) will be expressed as frequencies and percentages. Comparisons between groups will be performed using independent t-tests or Mann-Whitney U tests for continuous variables, and chi-square or Fisher exact tests for categorical variables, with 95% confidence intervals reported. The effect of the intervention on primary and secondary AF-related outcomes will be examined using regression models with and without adjustment for baseline covariates. Formal hypothesis testing is not the primary focus. All analyses will be conducted in R (version 4.5.0), with statistical significance defined as a two-sided p-value <0.05.

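### Section 2.4 inflates the retention sample for 20% dropout, although dropout is the failure event of that endpoint and 20% dropout is exactly the 80% threshold; the stated 80% power does not apply there

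*Protocol article*

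**What the plan says.** Section 2.4 (Sample size) says that the pilot is sized to estimate feasibility parameters, and derives the numbers from "one-sided proportion tests (80% power, α=0.05) for retention and engagement". The one-sided form is justified by progression criteria "where only meeting or exceeding the thresholds is relevant". The result is given as: "Thresholds were retention ⩾80% and engagement ⩾70%, yielding 62 and 56 participants, respectively". It continues: "allowing for 20% dropout, the final target was 76 (38 per group"). No null proportion and no assumed true proportion is stated.

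Section 2.9.1 defines the endpoint as "retention rate (participants completing the 3-month follow-up"). The last paragraph of the Introduction says that the trial will quantify the feasibility rates and "compare each against pre-specified progression thresholds (retention ⩾80%, engagement ⩾70%), constituting the primary outcomes". Section 2.10.1 adds: "Formal hypothesis testing is not the primary focus". The Discussion makes the predefined feasibility criteria the basis for going on to a definitive multi-center trial.

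**The concern.** Two things in Section 2.4 do not fit together.

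- **Dropout is used as a loss of data.** On the stated definition, a participant who drops out before 3 months is a non-retained participant. That participant is observed, counts as a failure and stays in the denominator. Inflating a sample for dropout makes sense when dropouts cannot be evaluated, and for retention they can.
- **The dropout allowance sits on the threshold.** A 20% dropout rate is 80% retention. A one-sided test of whether retention exceeds 80% has power equal to its own size when true retention is 80%. A claim of 80% power therefore needs true retention well above 80%, and the section names no such value.

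Retention is a primary outcome and a progression criterion. A reader who takes the 80% power at face value will misjudge how likely the pilot is to meet or demonstrate that criterion if dropout is near the figure the plan allows for.

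**Working it through.** **Inputs.** From Section 2.4: one-sided α = 0.05, power 80%, retention threshold 80%, base sample 62, dropout allowance 20%, final sample 76. From Section 2.9.1: retained means completed the 3-month follow-up, so retention = 1 − dropout.

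**1. Reproducing 62.** Only one proportion (80%) is stated, so 62 cannot be reproduced from the stated inputs alone. It can be reached in more than one way:

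- *80% as null, normal approximation.* n = [1.645·√(p0(1−p0)) + 0.842·√(p1(1−p1))]² / (p1−p0)². With p0 = 0.80, p1 = 0.91 gives 67 and p1 = 0.92 gives 55, so 62 corresponds to p1 of about 0.914.
- *80% as null, arcsine formula.* n = [(1.645 + 0.842)/h]², with h = |2·asin√0.91 − 2·asin√0.80| = 0.318, gives 61.2, rounded up to 62.
- *80% as null, exact binomial.* With n = 62, 56 retained are needed, and 80% power requires true retention of about 92.3%.
- *80% as alternative, exact binomial.* Against an assumed null of 65%, n = 62 rejects at 47 or more, with size 4.6% and power 83.8% at 80%. This also fits 62.

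**2. From 62 to 76.** 62/0.8 = 77.5, and 62 × 1.2 = 74.4, which becomes 75 and then 76 for equal arms. The difference from 78 is two participants, a matter of rounding convention, and is not part of this point.

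**3. Dropout against threshold.** 1 − 0.20 = 0.80, and 76 × 0.80 = 60.8 retained. The allowance and the threshold are the same number.

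**4. What 76 delivers with everyone in the denominator (exact binomial).**

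*80% as null.* The critical value is the smallest r with P(X ≥ r | 76, 0.80) ≤ 0.05. P(X ≥ 66) = 0.084 and P(X ≥ 67) = 0.045, so r = 67, or 88.2%.

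*Observed-rate rule.* 60/76 = 78.9% and 61/76 = 80.3%, so passing means 61 or more.

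| True retention | Test against 80%: P(X ≥ 67) | Observed rate at least 80%: P(X ≥ 61) |
|---|---|---|
| 80% | 4.5% | 54.6% |
| 85% | 27.9% | 90.2% |
| 90% | 77.4% | 99.7% |

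For the test, 80% power is reached at true retention of about 90.3%, that is, dropout below 10%.

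*80% as alternative, null 65% (assumed).* With 76, rejection occurs at 57 or more, and 57/76 = 75.0%. Power at true 80% is 88.9%, but the test can reject with observed retention below 80%, so rejection does not show that the threshold is met.

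**5. Precision.** Half-width of a 95% interval at 80% retention with 76: 1.96 × √(0.80 × 0.20/76) = 0.090, about ±9 percentage points.

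**The case against.** A reader might infer that the trial has only about 5% power for retention. The documents do not support that without conditions, for four reasons.

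- **The null is not stated.** The 5% holds only if 80% is the null. The number 62 also fits 80% as the alternative against about 65%, where power at 80% retention is above 80%. This stands as a reason to attach the condition. It does not rescue the section: no 65% figure appears in the article, and that test would not show that retention meets 80%, which is what the one-sided form is said to reflect.
- **20% is an allowance.** Section 2.4 allows for 20% dropout and does not say it expects it. Power at the null always equals the size of the test, so the 5% comes from reading the allowance as the truth. This stands, although 20% is the only dropout figure in the plan.
- **The design can have 80% power.** With all 76 counted, power exceeds 80% once true retention is about 90.3% or more; at 91.4%, the value behind 62 under the normal approximation, it is 88%. It would be wrong to say that 76 cannot deliver the stated power. What is missing is the retention it depends on.
- **Progression may not rest on a test.** The Introduction compares rates with thresholds, and Section 2.10.1 plays down formal testing. Nothing says that progression requires rejecting 80% at one-sided 5%. Under an observed-rate rule the chance of passing is 55% at true 80%, and a chance near one half exactly at the threshold is inherent in any such rule. This stands too, but 55% is not the stated 80% either.

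**Conclusion.** The point holds in conditional form. Two parts hold on any reading of the test: the retention sample should not be inflated for dropout, since dropout is the failure event of that endpoint, and the 20% allowance places retention exactly on the 80% threshold. No reading examined makes the stated 80% power apply to meeting that threshold at 20% dropout. With 80% as the null, power there is at most 5% (exact 4.5%). With 80% as the alternative, power is adequate but for a different claim. With an observed-rate rule, the chance of passing is 55%.

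These figures assume independent participants, all 76 in the denominator, both arms pooled and, for the second reading, an assumed null of 65%. Because the pilot aims at estimation, 76 can give 80% power at true retention of about 90.3% or more, and the remedy is wording only, this is a should-fix.

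**What to change.** In Sections 2.4 and 2.9.1:

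1. Define retention over all 76 randomised participants, with dropouts counted as not retained, and remove the dropout inflation from the retention calculation.
2. State the null proportion and the assumed true retention that gave 62, and reconcile them with the 20% allowance.
3. Either tie the 80% power to true retention of about 90% or more (exact value about 90.3% with 76, if 80% is the null), or replace the power statement with the precision that 76 gives, about ±9 points at 80% retention.
4. State whether progression on retention is judged on the observed rate or by the one-sided test. Leave the criterion at 80% or more. The 67 of 76 above describes the test and should not become a new progression requirement.

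The cost is rewording. The sample stays at 76 and no patients are added. If the test is kept, the power reported at 80% to 85% retention will look less favourable than the present text suggests.

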**Methods and analysis:**

PROMBot-HSM-AF is a single-center, open-label, randomized controlled pilot (feasibility) trial with two parallel groups, conducted at Santa Marta Hospital, Lisbon, Portugal. Seventy-six patients undergoing AF ablation will be randomized in a 1:1 ratio to either chatbot-supported follow-up or standard care. The primary feasibility parameters are: recruitment rate (proportion of eligible patients consenting), retention rate at 3 months, and chatbot engagement rate (proportion of chatbot prompts answered). Acceptability and usability will be assessed using behavioral indicators (engagement and retention), the System Usability Scale (SUS), the Post-Study System Usability Questionnaire (PSSUQ), and semi-structured interviews with patients and healthcare professionals. Quantitative data will be analyzed descriptively with exploratory between-group comparisons. Semi-structured interviews with patients and healthcare professionals will be analyzed using thematic content analysis.

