#### Control group

2.7.2

Participants allocated to the control group receive standard post-ablation care as delivered at Santa Marta Hospital, which includes structured discharge instructions with written educational materials about post-ablation care, scheduled follow-up appointments at 1 month and 3 months post-discharge, open access to the cardiology clinic telephone line during working hours for clinical concerns, and a 24-h hospital telephone service for urgent medical issues. Control group participants do not receive remote monitoring between scheduled appointments.

Both intervention and control groups complete identical standardized assessments at baseline (pre-discharge) and 3 months post-ablation. The timing of data collection activities is outlined in Table 1.

**Table 1 T1:** Schedule of enrollment, interventions, and assessments for the PROMBot-HSM-AF trial.

TRIAL PERIOD		Enrollment	Post-randomization				
Timepoint	Arm	⩽ day 0	Day 0	M1	M2	M3	M12
Target window		up to day 0	day 0	30±3 d	60±5 d	90±5 d	365±14 d
ENROLLMENT							
Eligibility screen	I+C	X					
Informed consent	I+C	X					
Randomization/allocation	I+C		X				
INTERVENTIONS							
PROMBot-HSM-AF	I			X	X	X	
Standard care	C		X	X	X	X	
PRIMARY OUTCOMES (FEASIBILITY)							
Recruitment rate	I+C	X	X				
Retention rate	I+C					X	
Engagement rate	I			X	X	X	
BASELINE CHARACTERISTICS							
Demographics	I+C		X				
AF history & comorbidities	I+C		X				
Procedure-related characteristics	I+C		X				
CLINICAL OUTCOMES (HOSPITAL-REPORTED)							
AF recurrence (AAD/cardioversion/repeat ablation)	I+C			X	X	X	X
Complications (readmission, ED visit, thromboembolism, major bleeding, tamponade)	I+C			X	X	X	X
All-cause mortality	I+C						X
Cardiology/internal-medicine consultations	I+C					X	X
Diagnostic tests (ECG, Holter)	I+C			X	X	X	X
PROMs							
AFEQT	I+C		X			X	
ESC quality-indicator items (weekly, rotating)	I			X	X	X	
Symptom checklist	I			X	X	X	
Medication adherence	I			X	X	X	
BIOSIGNALS							
Body mass	I			X	X	X	
Blood pressure	I			X	X	X	
Heart rate	I			X	X	X	
Step count	I			X	X	X	
ACCEPTABILITY & USABILITY							
Patient experience (SUS, PSSUQ, interview)	I					X	
Healthcare-professional experience (SUS, PSSUQ, interview)	HCP					X	

The schedule follows the SPIRIT figure convention (34).

M, month; d, days. Arm: I = intervention; C = control; HCP = healthcare professionals.

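### Section 2.4 says 76 allows for 20% dropout from 62, but it allows for at most 18.4%; the sentence needs restating and the target can stay

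*Protocol article*

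**What the plan says.** Section 2.4 of the protocol article explains the size in three steps.

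- The method: "sample sizes were derived from one-sided proportion tests (80% power, α=0.05) for retention and engagement".
- The results before any allowance: "Thresholds were retention ⩾80% and engagement ⩾70%, yielding 62 and 56 participants, respectively".
- The allowance and the target: "allowing for 20% dropout, the final target was 76 (38 per group".

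The section gives no formula for turning 62 into 76. The abstract repeats the total as the headline size: "Seventy-six patients undergoing AF ablation will be randomized in a 1:1 ratio to either chatbot-supported follow-up or standard care".

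Two other places bear on how the figure should be read. Section 2.9.1 defines the outcome behind the 62 as "retention rate (participants completing the 3-month follow-up". Table 1 assesses retention in both arms and engagement in the intervention arm only.

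**The concern.** Both inputs (62 and 20%) and the output (76) stand in the same sentence, so the step between them can be checked directly, and the usual calculation does not give 76. A dropout allowance normally means that the required number remains after the stated share of those enrolled is lost. That calls for division by one minus the dropout proportion. The figure printed agrees instead with adding 20% to the required number, which gives a smaller allowance than the one named.

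What is at stake is the accuracy of the account given for the trial's headline sample size. A reader who takes the sentence at face value will believe that the trial can lose a fifth of its participants and still have 62 completers, which is not so.

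**Working it through.** **Inputs, all from section 2.4.** Required number for retention: 62 (31 per group under 1:1 allocation). Required number for engagement: 56. Dropout: 20%. Stated target: 76, or 38 per group. The 62 and 56 are taken as given. They cannot be re-derived, because the section gives one proportion for each test and not the null and alternative pair.

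**Which requirement sets the total.** 56/0.80 = 70, which is below 76. The 62 is therefore the binding figure.

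**Reproducing 76.** Adding 20% to each arm: 31 × 1.2 = 37.2, rounded up to 38 per group, and 2 × 38 = 76. This returns the printed figure exactly. Applied to the total, the same rule gives 62 × 1.2 = 74.4, rounded up to 75, or to 76 if an even number is wanted.

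**Standard allowance.** Number to enrol = required number / (1 − dropout).

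- Total: 62/0.80 = 77.5, rounded up to 78.
- Per group: 31/0.80 = 38.75, rounded up to 39, and 2 × 39 = 78.
- Difference from the stated target: 78 − 76 = 2 patients, and 2/76 = 2.6%.

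**Reverse check, which needs no inflation formula.**

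- 76 × 0.80 = 60.8, so about 61 remain, against 62.
- Largest dropout at which 76 keeps 62: (76 − 62)/76 = 14/76 = 18.4%.
- Before rounding, adding 20% covers a loss of 12.4/74.4 = 16.7% of those enrolled. Rounding up to 76 brings this to 18.4%.

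**Effect on precision.** As an illustration, assume an observed proportion of 80% and use the normal approximation, with 95% half-width = 1.96 × √(0.8 × 0.2/n).

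| n | Half-width (percentage points) |
|---|---|
| 76 | 9.0 |
| 78 | 8.9 |
| 61 | 10.0 |
| 62 | 10.0 |

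The two patients make no practical difference, whether all randomised participants or only completers are counted.

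**Does the retention analysis fall short?** The 62 belongs to retention, the proportion of participants who complete 3 months. Someone who drops out is a failure for that outcome and stays in the denominator. Table 1 assesses retention in both arms, so the denominator is naturally all 76 randomised, and 76 − 62 = 14 above the requirement.

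**The case against.** The strongest defence is that section 2.4 names no formula. Allowing for 20% dropout can loosely mean adding 20%, and on that convention 76 comes out exactly, within 2 patients of the standard answer. This stands to the extent that the figure is not arbitrary and the slip is small. It does not make the allowance right. Dropout is ordinarily a share of those enrolled, and the article's own retention criterion of 80% uses that denominator. On that footing 76 covers 18.4%, and rounding does not turn 77.5 into 76.

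A reader might go further and infer that the trial is under-enrolled, with fewer than the 62 it needs. The documents do not support that. The 62 is stated as a number of participants for a retention test, and dropouts are the event that test counts. On the definition in section 2.9.1 all 76 are analysed and there is no shortfall. Nor does engagement create one on the section's own terms, since 56 inflates only to 70.

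A reader might also conclude that the target should rise to 78. That does not follow either, because the retention calculation needs no dropout allowance. Table 1 does confine engagement to the intervention arm ("Engagement rate I X X X"), where 38 participants are available against the stated 56. That is a separate question, and one more patient per group would not settle it.

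**Conclusion.** The sentence is wrong as written, in a minor way. A target of 76 does not provide a 20% allowance on 62. It provides at most 18.4%, and at 20% dropout about 61 would remain. The figure consistent with a full 20% allowance is 78, a difference of 2 patients (2.6%).

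The conclusion assumes that 62 is correct as stated and that dropout means a share of those enrolled. It concerns the explanation of the sample size, not its adequacy for retention, which is met with all 76 randomised in the denominator. Precision is unaffected for practical purposes.

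**What to change.** Keep 76 and restate the last step of section 2.4, for example: *Retention will be estimated on all 76 randomised participants, which exceeds the 62 required. For outcomes that need completers, 76 keeps 62 with up to about 18% dropout; 20% dropout would leave about 61.*

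This separates the two uses of the number and drops the suggestion that retention itself needs a dropout allowance. The cost is one sentence, with no extra patients and no change to the design or analysis.

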### Randomization and allocation concealment

2.5

Participants will be randomly assigned to the intervention or control group using computer-generated random numbers in permuted blocks of variable size (4 to 6) to maintain allocation concealment. Randomization will be stratified by AF type (paroxysmal vs persistent) to ensure balance between groups, as AF type is a recognized prognostic factor for recurrence after catheter ablation (29). Allocation sequences will be generated by a statistician not involved in participant recruitment. Allocation concealment will be maintained through sequentially numbered, opaque, sealed envelopes prepared by personnel independent of the recruitment process, opened only after eligibility confirmation and completion of baseline assessments.

### Blinding

2.6

Due to the nature of the intervention, it is not feasible to blind participants or healthcare professionals providing care. However, outcome assessors conducting medical record reviews for clinical endpoints (e.g., hospitalizations, cardiovascular events) will be blinded to group allocation where possible. Statistical analyses will be conducted by a researcher blinded to group assignment until completion of primary analyses. Participants will be instructed not to disclose their group allocation during follow-up assessments conducted by blinded assessors.

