In the first month, chatbot interactions will occur daily, focusing on post-ablation symptom surveillance and medication adherence. After that, the cadence will taper to reduce burden in later weeks while maintaining essential monitoring. Chatbot prompts will remain open for 24 h, after which nonresponses will be recorded as missing data. A study nurse or physician will review patient entries weekly and may proactively contact participants reporting concerning symptoms or lapses in engagement. PROMBot-HSM-AF will not replace routine follow-up; all patients will continue standard clinical care, with chatbot data available to the study clinical team to complement or inform consultations at the treating cardiologist’s discretion.

At the end of the 3-month follow-up period, all participants will undergo post-intervention assessments during a routine hospital visit. If necessary, these assessments will be conducted via secure videoconference. The PROMs will focus on the effect of AF on health-related quality of life. Participants in the intervention group will also complete validated measures of usability and perceived usefulness. They will also take part in a brief semi-structured interview to share their experience of using the chatbot. Semi-structured interviews will also be conducted with healthcare professionals directly involved in patient care (e.g., cardiologists, nurses, and technicians). These interviews are intended to elicit qualitative insights regarding their experience with the chatbot-based intervention, as well as their perceptions of its usability, clinical relevance, and impact on workflow integration.

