#### Qualitative data

2.10.2

Qualitative data related to the process and outcomes of the intervention will be analyzed using thematic content analysis. The analysis framework will integrate topics from the semi-structured interview guide with themes that emerge inductively during transcript familiarization. All interviews will be audio-recorded and transcribed verbatim using transcription software to capture participants’ responses. Two researchers will independently code the data, with discrepancies resolved through discussion to ensure coding reliability. Key themes will be illustrated with anonymized quotations. A purposive subsample of participants (10-15 from the intervention arm) (41, 42) will be interviewed to gain in-depth insights into usability, engagement, and perceived outcomes of the intervention.

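### Section 2.6 refers to follow-up assessments by blinded assessors, but the procedures describe no such assessment with participant contact, so the month-3 AFEQT comparison should be presented as open-label self-report

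*Protocol article*

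**What the plan says.** Section 2.6 (Blinding) concedes that "it is not feasible to blind participants or healthcare professionals providing care". It then names one group of blinded assessors: "outcome assessors conducting medical record reviews for clinical endpoints (e.g., hospitalizations, cardiovascular events) will be blinded to group allocation where possible". It adds a blinded analyst and closes with "Participants will be instructed not to disclose their group allocation during follow-up assessments conducted by blinded assessors".

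Section 2.7.1 describes month 3: "all participants will undergo post-intervention assessments during a routine hospital visit", with videoconference as a fallback. It continues: "Participants in the intervention group will also complete validated measures of usability and perceived usefulness". On the interview it says: "They will also take part in a brief semi-structured interview to share their experience of using the chatbot". Section 2.10.2 gives a narrower scope for the interviews: "A purposive subsample of participants (10-15 from the intervention arm".

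In Table 1 (section 2.7.2) AFEQT is scheduled for both arms at day 0 and month 3, while the row beginning "Patient experience (SUS, PSSUQ, interview" is for the intervention arm only, at month 3. The text above that table says that the two arms have identical assessments at baseline and 3 months. Section 2.9.4 says that all PROMs and biosignals are gathered through the chatbot. The limitations paragraph of the Discussion claims only partial mitigation from assessor blinding, and only for objective clinical endpoints.

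**The concern.** The closing sentence of section 2.6 makes sense only if a blinded assessor meets participants. A record reviewer does not, and the article describes nobody else who could be meant. A reader who looks for such an assessment will arrive at AFEQT, because it is the only patient-reported measure scheduled in both arms at follow-up.

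The stake is how the AFEQT comparison is read. Section 2.1 hypothesises a more favourable AFEQT trend under the chatbot, and the aims in the Introduction say that between-group differences will help to plan a definitive trial. Those who plan that trial need to know that the estimate comes from unblinded respondents with no described masking of the person collecting it. They also need to know whether the circumstances of collection differed between arms for reasons that could have been avoided.

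**Working it through.** The plan gives no figure on this point to reproduce. The check sets the relevant places side by side.

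1. **Who is blinded.** Section 2.6 names record reviewers, where possible, and the analyst. Section 2.9.3 takes clinical outcomes from hospital records. Neither role has any described contact with participants, so the non-disclosure instruction protects nobody whom the article identifies.

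2. **What both arms do with participant contact after randomization.** In Table 1 the clinical outcomes are hospital-reported. The weekly quality-indicator items, symptom checklist, medication adherence, biosignals and patient usability measures are all for the intervention arm only. AFEQT at month 3 is the one patient-reported measure common to both arms. It is the natural referent of the sentence, although section 2.6 does not name it.

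3. **What the month-3 forms reveal.** SUS and PSSUQ apply to the whole intervention arm and to no control. A person who handles the full set therefore learns the allocation in either arm, from the presence or absence of these forms. The interview reveals less. With the planned 38 per group (section 2.4), 10/38 = 26% and 15/38 = 39% of the intervention arm would be interviewed under section 2.10.2. Section 2.7.1 reads as if all of them were. The argument does not need the interview, because the two questionnaires suffice.

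4. **Who is likely to be present.** The setting is a routine visit. Section 2.6 concedes that treating professionals are unblinded, and section 2.7.1 makes chatbot data available to the study clinical team for consultations. That unblinded staff administer AFEQT is an inference. The article does not say who does so, or in what order the instruments are given.

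5. **How AFEQT is collected.** If section 2.9.4 is taken literally, intervention patients answer AFEQT through WhatsApp with no assessor, and controls must use some other mode. If sections 2.7.1 and 2.7.2 are taken literally, both arms answer at the hospital visit. The two accounts cannot both hold for controls. Under the first, the mode differs between arms. Under neither is a blinded assessor described.

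6. **The scope claimed elsewhere.** The Discussion confines the benefit of assessor blinding to objective clinical endpoints. That agrees with the record-review statement in section 2.6 and leaves the closing sentence of that section as the outlier.

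**The case against.** A reader might infer that the protocol claims blinded assessment of AFEQT and that this blind is bound to fail. The documents support neither part. Section 2.6 does not mention AFEQT, the Discussion limits blinding to objective endpoints, and the trial is labelled open-label. The disputed sentence covers only whatever assessments blinded assessors conduct. Nothing states who administers AFEQT or in what order, so separate staff, or AFEQT taken first, would be compatible with the text and could keep an assessor masked. All of this stands, and it is why the point is lack of support in the described procedures, not impossibility.

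A second objection is that AFEQT respondents are themselves unblinded, so masking whoever hands over the form would remove only part of any bias. That also stands. It is a reason to call AFEQT unblinded self-report plainly, and it means that the visit order proposed below removes an avoidable difference between arms but does not make the outcome blinded.

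Third, AFEQT comparisons are secondary, exploratory and hypothesis-generating, and the Discussion already acknowledges observation bias. This limits the importance of the point. The 5-point AFEQT change that section 2.9.4 calls meaningful should not be used to suggest how large a bias might be, since it says nothing about that.

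Finally, visit logistics are commonly left to the full protocol. The absence of such detail is no fault. What remains is a positive statement about blinding that the article's own procedures do not support, and a statement on PROM collection that cannot apply to controls.

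**Conclusion.** The point holds in a limited form. The closing sentence of section 2.6 presupposes a blinded assessment with participant contact that the procedures do not describe. The month-3 visit as described, with usability questionnaires in one arm only, does not support assessor blinding for AFEQT, and the stated mode of PROM collection cannot be the same in both arms.

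The size of any resulting bias cannot be derived from the document. Recruitment, retention and engagement, the primary outcomes, are unaffected. The conclusion rests on the article's description being complete as to who is blinded. If the full protocol names a separate, masked assessor for a defined assessment, what remains is to say so in section 2.6 and to reconcile the mode of AFEQT collection.

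**What to change.** 1. In section 2.6, limit the blinding claim to record review of clinical endpoints, keeping the existing qualifier, and to the analyst.
2. Delete the non-disclosure sentence, or tie it to a specified assessment and to an assessor who does not handle the chatbot questionnaires.
3. Describe AFEQT as an unblinded, self-reported outcome.
4. Have AFEQT self-completed in the same mode in both arms at month 3, before the consultation and before SUS, PSSUQ and interview.
5. Reconcile section 2.9.4 with section 2.7.1 and with section 2.7.2 and its Table 1 on how AFEQT is collected in controls. In the same edit, align the interview wording of section 2.7.1 with the subsample in section 2.10.2.

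The cost is a visit-order instruction, a few sentences of text and a less favourable blinding statement. No extra staff are needed unless the sentence is kept and a separate assessor has to be named.
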